Preliminary clinical data with Ad35.CS.01 are available from a randomized, double-blind Phase I study carried out by the US National Institute of Allergy and Infectious Diseases, which evaluated the safety, tolerability and immunogenicity of increasing doses ( $10^8$  to  $10^{11}$  vp) of Ad35.CS.01. A total of 60 subjects (14, 15, 15 and 16 at the  $10^8$ ,  $10^9$ ,  $10^{10}$ , and  $10^{11}$  vp dose level, respectively) received vaccine, 12 subjects received a saline placebo at 0, 1, and 6 months.

The safety and tolerability of the Ad35.CS.01 malaria vaccine was evaluated through the assessment of local and systemic solicited reactions, unsolicited adverse events and clinical laboratory parameters.

The local tolerability of the vaccine was acceptable at all doses. The  $10^{11}$  vp dose was more frequently associated with pain of mild to moderate severity than the lower doses. The frequency of erythema was dose-dependent as well, but all the events were consistently mild across all doses. All solicited local reactions resolved without sequelae.

Systemic tolerability was assessed through the following solicited symptoms and signs: headache, malaise, myalgia, chill, nausea, vomiting and fever. Symptoms were scored

daily by subjects on diaries for 14 days after each dose. Results are summarized in [Table 1](#).

**Table 1** Number (%) of subjects with solicited systemic reactions, by maximal severity, after each injection

|             |          | Placebo
(N=12) | Ad35.CS.01 10 
(N= 14) | Ad35.CS.01 10 
(N=15) | Ad35.CS.01 10 
(N=15) | Ad35.CS.01 10 
(N=16) |
|-------------|----------|-------------------|---------------------------------------|--------------------------------------|---------------------------------------|---------------------------------------|
| First dose  | Mild     | 1 (8)             | 3 (21)                                | 2 (13)                               | 4 (27)                                | 6 (38)                                |
|             | Moderate | 2 (17)            | 2 (14)                                | 0 (0)                                | 1 (7)                                 | 5 (31)                                |
|             | Severe   | 0 (0)             | 0 (0)                                 | 0 (0)                                | 1 (7)                                 | 2 (13)                                |

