#### **5.4.2. Risks to the subjects and precautions to minimize risk**

##### **5.4.2.1. Risks associated with vaccination and mitigation of risks**

###### **Ad35.CS.01 vaccine**

As with many vaccines, the Ad35.CS.01 vaccine has shown mild to moderate injection site pain, swelling, or discomfort. There may also be some bruising or discoloring and rarely infection might occur. Other common side effects are fever, headaches, chills, nausea, vomiting, body aches, numbness or muscles weakness and tiredness. These reactions are usually greatest within the first 24-72 hours after vaccination and last 1-2 days. There is a rare possibility of an allergic reaction to the vaccine. As with any vaccine, unexpected serious adverse events, including allergic reactions to the vaccine components, may occur, although this has not been reported in prior studies with Ad35.CS.01.

In a previous study of consecutive administration of 3 doses of Ad35.CS.01 to various dose levels, some vaccinated individuals reported paresthesia and weakness in the vaccinated arm (refer to Section 1.1.2 for more details). The occurrence of new neurological symptoms after immunization will be monitored in this study in a standard way, using a standard neurological examination form assessing central and peripheral nervous systems, motor and sensory functions upon D0, D6 and D28 post first immunization ([Appendix B](#)).

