###### **RTS,S/AS01B vaccine**

The most frequent adverse reactions observed in previous clinical trials using the RTS,S antigen and AS01B adjuvant system include pain, swelling, erythema, and tenderness at the site of injection, and systemic symptoms such as low-grade fever and short-term flu-

like symptoms: fatigue, myalgia, headache, malaise. As with any vaccine, unexpected serious adverse events, including allergic reactions to the vaccine components, may occur, although this has not been reported in prior studies with RTS,S or the adjuvant.

Sometimes people who get vaccines with the adjuvant system used in this study report illnesses called autoimmune diseases as side effects. These are serious diseases. They result from an attack of the immune system on the body's own tissues. Examples of autoimmune diseases, or their symptoms, include nervous system disorders, inflammation of the blood vessels, impaired blood clotting, skin rashes, arthritis, thyroid gland disease, muscle pains or weakness, liver disease and kidney disease. It is possible that vaccines with this adjuvant system caused these side effects, but we do not yet know - because these same diseases can also occur in people who get other vaccines, or no vaccines at all.

As outlined above, the volunteers will be monitored closely during their participation in this study. The study vaccines have been prepared according to Good Manufacturing Practices (GMP). The vaccines will be administered under the supervision of an investigator and nurses equipped with drugs and equipment to immediately treat anaphylaxis.

While the study is observer-blinded, the investigator, or a person designated by the investigator, may request unblinding of a subject's treatment code in order to provide specific vaccine information for the study team or for health care providers caring for the volunteer subject(s). Refer to Section 8.8 for the procedure of emergency unblinding.

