**5.4.4.1.2. Data review by the SMC between vaccine doses (for each Cohort separately only)**

Listings will be produced and reviewed once all subjects have been followed up for 7 days post vaccination (day 0 to day 6) after vaccination dose 1 and dose 2, prior to authorizing progression to dose 2 and dose 3, respectively. No stopping rule will be pre-defined when considering progression from dose 1 to dose 2, as only RTS,S/AS01B will be administered as from dose 2, considering that RTS,S/AS01B has a well characterized, favourable safety profile, with a pediatric formulation currently in Phase 3 evaluation. As RTS,S/AS01B has never been administered before in individuals vaccinated with Ad35.CS.01, and considering that past immunization with Ad35.CS.01 may influence the reactogenicity to subsequent RTS,S/AS01B, stopping rules will be pre-defined when considering progression from dose 2 to dose 3.

The following listings will be produced and reviewed by the SMC when considering dose 1 to dose 2 and dose 2 to dose 3 progression:

- All reactogenicity data, presented by dose, all and grade 3, relatedness assessment (all and grade 3), tabulated by group
- All laboratory values and laboratory abnormalities estimated to be related to vaccination, presented according to protocol toxicity grading, tabulated by group
- All unsolicited events presented by individual events (separately, Serious Adverse Events and non serious Adverse Events), including study group, last vaccine received, time to onset, relatedness assessment, severity grade, outcome, decision to withdraw from further investigational product administration
- All unsolicited events (separately, Serious Adverse Events and non serious Adverse Events) presented as cumulative tables by group

- Results of standardized neurological examinations tabulated by group

The following pre-defined stopping rules will apply when considering progression from dose 2 to dose 3:

- Solicited local adverse events:
  - More than 25% of subjects vaccinated with RTS,S/AS01B after having received Ad35.CS.01 develop a Grade 3 solicited local adverse event beginning within 2 days after vaccination (day of vaccination and one subsequent day) and persisting at Grade 3 for > 2 consecutive days
- Solicited systemic adverse events:

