  - more than 25% of subjects vaccinated with RTS,S/AS01B after having received Ad35.CS.01 develop a Grade 3 solicited systemic adverse event beginning within 2 days after vaccination (day of vaccination and one subsequent day) and persisting at Grade 3 for > 2 consecutive days.

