**5.4.4.1.3. Cohort A data review by the SMC prior to vaccinations in Cohort B and Cohort C:**

An interim unblinded SMC report including all available safety and reactogenicity data, will be produced by an independent statistician according to an agreed pre-defined Report and Analysis Plan, after the Cohort A has completed the one month post challenge visit. The SMC will review this report prior to authorizing vaccinations to proceed in Cohort B and Cohort C. Vaccination of the next cohort of study participants can be put on hold by the SMC if either of the following sets of holding criteria described below is met:

*Holding rules*

- Solicited local adverse events:
  - More than 25% of Ad35.CS.01 doses are followed by Grade 3 solicited local adverse event beginning within 2 days after Ad35.CS.01 vaccination (day of vaccination and one subsequent day) and persisting at Grade 3 for > 2 consecutive days
  - More than 25% of first doses of RTS,S/AS01B in subjects having received Ad35.CS.01 are followed by Grade 3 solicited local adverse event beginning within 2 days after vaccination (day of vaccination and one subsequent day) and persisting at Grade 3 for > 2 consecutive days
  - More than 25% of second doses of RTS,S/AS01B in subjects having received Ad35.CS.01 are followed by Grade 3 solicited local adverse event beginning within 2 days after vaccination (day of vaccination and one subsequent day) and persisting at Grade 3 for > 2 consecutive days
- Solicited systemic adverse events:
  - More than 25% of Ad35.CS doses are followed by Grade 3 solicited systemic adverse event estimated to be related to vaccination beginning within 2 days

after Ad35.CS.01 vaccination (day of vaccination and one subsequent day) and persisting at Grade 3 for > 2 consecutive days

- More than 25% of first doses of RTS,S/AS01B in subjects having received Ad35.CS.01 are followed by Grade 3 solicited systemic adverse event estimated to be related to vaccination beginning within 2 days after vaccination (day of vaccination and one subsequent day) and persisting at Grade 3 for > 2 consecutive days
- More than 25% of second doses of RTS,S/AS01B in subjects having received Ad35.CS.01 are followed by Grade 3 solicited systemic adverse event estimated to be related to vaccination beginning within 2 days after vaccination (day of vaccination and one subsequent day) and persisting at Grade 3 for > 2 consecutive days

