- Unsolicited adverse events
  - a serious adverse event considered related to vaccination occurs in a study participant from the Ad35.CS.01 – RTS,S/AS01B – RTS,S/AS01B group
  - more than 25% of subjects from the Ad35.CS.01 – RTS,S/AS01B – RTS,S/AS01B group develop any Grade 3 unsolicited adverse event considered related to vaccination and persisting at Grade 3 for > 2 consecutive days.
- Standard neurological evaluation
  - more than 10% of subjects from the Ad35.CS.01 – RTS,S/AS01B – RTS,S/AS01B group develop abnormal neurological symptoms captured by standardized neurological evaluation ([Appendix B](#)).
- Laboratory adverse events
  - more than 25% of subjects from the Ad35.CS.01 – RTS,S/AS01B – RTS,S/AS01B group develop any Grade 3 laboratory adverse event considered related to vaccination.
  - more than 10% of subjects develop hematuria, not taking into account menstruating females if the hematuria coincides with their regular monthly time for their period or urinary tract infection.

If a holding rule has been met, vaccination of subjects in the subsequent cohort will only start if GSK, Crucell, MVI and investigators agree to it, following discussions with the SMC. All IRBs will be notified if a holding rule is activated or released after SMC review.

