**Table 23 Solicited local adverse events**

|                            |
|----------------------------|
| Pain at injection site     |
| Redness at injection site  |
| Swelling at injection site |

The following general adverse events will be solicited:

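### Minor, cheap improvement: myalgia, named as a frequent RTS,S/AS01B reaction, is not on the solicited list, so it has no Day 0-6 row and, when isolated, cannot count toward the dose 2 to dose 3 group rule

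*Protocol*

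**What the plan says.** Protocol Section 8.1.3 leads into Table 24 with "The following general adverse events will be solicited". The table lists fatigue, fever, gastrointestinal symptoms, headache and chills. Its footnote limits gastrointestinal symptoms to nausea, vomiting, diarrhoea and abdominal pain. Table 23 covers injection-site pain, redness and swelling. Table 27 grades these same symptoms. Myalgia appears in none of the three, and Section 8.1.1 makes every event outside Section 8.1.3 unsolicited.

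Elsewhere the protocol treats myalgia as expected. Section 5.4.2.1 includes it among the most frequent RTS,S/AS01B reactions ("like symptoms: fatigue, myalgia, headache, malaise") and says of Ad35.CS.01: "Other common side effects are fever, headaches, chills, nausea, vomiting, body aches, numbness or muscles weakness and tiredness". Section 1.1.2 reports of the earlier Ad35.CS.01 trial: "Systemic tolerability was assessed through the following solicited symptoms and signs: headache, malaise, myalgia, chill, nausea, vomiting and fever".

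The group rule for moving from dose 2 to dose 3 (Section 5.4.4.1.2) has two criteria, solicited local and solicited systemic. The systemic one is met when more than 25% of subjects given RTS,S/AS01B after Ad35.CS.01 "develop a Grade 3 solicited systemic adverse event beginning within 2 days after vaccination" that stays at Grade 3 for more than 2 consecutive days. There is no unsolicited criterion at this step.

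**The concern.** RTS,S/AS01B makes up five of the six scheduled doses across the two regimens (Table 22). One of its named frequent reactions is nevertheless not asked about by name after vaccination. Two things follow.

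First, the Day 0-6 solicited endpoint (Section 10.1) and its by-dose tables (Section 10.8.4) have no myalgia row. Myalgia is picked up through an open, non-leading question (Section 8.3.2.1), and under Section 10.6 a subject who does not report a symptom is analysed as not having had it. A direct by-dose comparison of graded myalgia between ARR and RRR therefore rests on weaker capture than the one for headache or fatigue.

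Second, Section 5.4.4.1.2 justifies the dose 2 to dose 3 rule by the possibility that Ad35.CS.01 priming changes the reactogenicity of the RTS,S/AS01B doses that follow. Isolated persistent Grade 3 myalgia after dose 2, which is a reaction of that kind, is outside the count.

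**Working it through.** **Text check.**

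| Symptom in the risk text or earlier trial | In Tables 24 and 27? |
|---|---|
| Fatigue or tiredness, headache, fever, chills | Yes |
| Nausea, vomiting | Yes, as gastrointestinal symptoms |
| Myalgia or body aches | No |

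The protocol asks about muscle aches by name only in the post-challenge hotel/inpatient phase (Section 5.4.3.5), which does not cover the days after vaccination.

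**Group rule trigger.** The rule is applied within each cohort, and Cohort A has 28 subjects per group (Section 5.4.3). More than 25% of n means floor(0.25n) + 1 subjects. For n = 28 this is 7 + 1 = 8. For n = 24 to 27 it is 6 + 1 = 7.

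**Effect of leaving myalgia out.** Two quantities are assumptions, because the protocol gives neither:

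- p: the true rate of qualifying persistent Grade 3 systemic reactions, myalgia included
- s: the share of those subjects whose only qualifying reaction is myalgia

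P(rule met) = 1 - BinomCDF(trigger - 1; n, p(1 - s)). For n = 28 and trigger 8:

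| p | s = 0 | s = 10% | s = 25% | s = 50% |
|---|---|---|---|---|
| 7% | 0.05% | 0.03% | 0.01% | <0.001% |
| 13% | 2.3% | 1.3% | 0.4% | 0.03% |
| 20% | 18% | 12% | 5% | 0.5% |
| 30% | 64% | 50% | 28% | 5% |
| 35% | 82% | 70% | 46% | 10% |

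The s = 0 column is also the chance of meeting the rule if myalgia were counted. The lower trigger raises the figures when fewer subjects receive dose 2. At p = 13% and s = 0, the chance is 2.3% at n = 28, 4.4% at n = 26 and 5.3% at n = 27. At p = 20% and n = 26, it is 25% for s = 0, falling to 17%, 8% and 1.2%.

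**What the protocol offers on p.** Table 1 gives severe systemic reactions after a first Ad35.CS.01 dose: 1/15 (7%, exact 95% CI 0.2% to 32%) at 10^10 vp and 2/16 (12.5%, exact 95% CI 1.6% to 38%) at 10^11 vp. These carry no persistence requirement and do not concern RTS,S/AS01B after priming. They are a loose guide only, and the intervals do not exclude 20% or more.

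**The case against.** The case for leaving the list alone is substantial.

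- **Committee review.** Section 5.4.4.1.2 states "Listings will be produced and reviewed once all subjects have been followed up for 7 days post vaccination". These listings include every unsolicited event with group, time to onset, relatedness and severity, and they are reviewed before dose 3 is authorised. This stands, although no numerical trigger attaches to unsolicited events at that step.
- **Other rules.** Related Grade 3 myalgia lasting more than 2 days stops further vaccination for that subject. The Cohort A review can hold later cohorts if more than 25% of the ARR group "develop any Grade 3 unsolicited adverse event considered related to vaccination and persisting at Grade 3 for > 2 consecutive days". The solicited systemic rules in that same review also require relatedness ("Grade 3 solicited systemic adverse event estimated to be related to vaccination beginning within 2 days after vaccination"), so causality gives solicited symptoms no advantage there. The investigator may also ask for a hold. All this stands, except that the Cohort A review follows challenge and cannot protect that cohort's own third dose.
- **Grading.** Section 8.3.2.2.1 grades unsolicited events 1 to 3 by effect on everyday activities, in substance the headache and fatigue scale. So myalgia is graded. What is lost is prompting by name and a place in the solicited count.
- **Preference.** Nothing in the protocol requires every named reaction to be solicited, and malaise is missing too. This is fair, and it is why the point is a suggested improvement.

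A reader might infer that the protocol contradicts itself, or that severe myalgia escapes all safety rules. Neither follows, given the routes above. A reader might also infer that myalgia faces a stricter causality test in the dose 2 to dose 3 rule. It does not: that rule has no unsolicited route at all.

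**Conclusion.** The point holds as a minor one. Myalgia is named as frequent, was solicited in the earlier Ad35.CS.01 trial, and is neither solicited nor given its own scale here. It therefore has no row in the Day 0-6 solicited endpoint, and isolated persistent Grade 3 myalgia cannot enter the one group rule that governs progression to dose 3. A subject who also has a qualifying Grade 3 fatigue, headache, chills, fever or gastrointestinal reaction is still counted.

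The effect on the group rule cannot be fixed from the protocol, because p and s are assumptions. If p is about 13% or lower, the rule is met at most about 2% to 5% of the time, with or without myalgia. A material loss needs p of about 20% or more together with a meaningful share of isolated myalgia.

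**What to change.** Add myalgia to Tables 24 and 27, the diary card and the eCRF, on the same 0-3 activity scale as headache and fatigue. It then counts in the 7-day solicited endpoint and in the solicited systemic rules on the same terms as the other solicited symptoms.

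The cost is one more item on a card already completed with the investigator on Days 1, 2, 3 and 6 (Section 5.6.3.9), an eCRF field and the table wording. The group rule becomes slightly easier to meet. Because the change touches a primary safety endpoint and a stopping rule, it needs a protocol amendment (Glossary) and IRB approval (Section 5.1). No visit, sample or staff is added.

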**Table 24 Solicited general adverse events**

|                                        |
|----------------------------------------|
| Fatigue                                |
| Fever                                  |
| Gastrointestinal symptoms † |
| Headache                               |
| Chills                                 |

†Gastrointestinal symptoms include nausea, vomiting, diarrhoea and/or abdominal pain.

Note: Temperature will be recorded once per day. Should additional temperature measurements be performed, the highest temperature will be recorded in the eCRF.

#### **8.1.4. Clinical laboratory parameters and other abnormal assessments qualifying as adverse events or serious adverse events**

Abnormal laboratory findings (e.g. clinical chemistry, haematology, urinalysis) or other abnormal assessments that are judged by the investigator to be clinically significant will be recorded as AEs or SAEs if they meet the definition of an AE, as defined in Section 8.1.1 or of a SAE, as defined in Section 8.1.2. Clinically significant abnormal laboratory findings or other abnormal assessments that are detected during the study or are present at baseline and significantly worsen following the start of the study will be reported as AEs or SAEs.

The investigator will exercise his or her medical and scientific judgement in deciding whether an abnormal laboratory finding or other abnormal assessment is clinically significant.

#### **8.1.5. AEs of specific interest**

##### **8.1.5.1. Potential immune-mediated diseases**

Potential immune-mediated diseases (pIMDs) are a subset of AEs that include autoimmune diseases and other inflammatory and/or neurologic disorders of interest which may or may not have an autoimmune aetiology. AEs that need to be recorded and reported as pIMDs include those listed in the table below.

However, the investigator will exercise his/her medical and scientific judgement in deciding whether other immune-mediated diseases have an autoimmune origin (i.e. pathophysiology involving systemic or organ-specific pathogenic autoantibodies) and should also be recorded as a pIMD.

**Table 25 List of potential immune-mediated diseases**

| Neuroinflammatory disorders                                                                                                                                                                                                                                                                                                                                                                                                                                                                                                                                                                                                                                                                                              | Musculoskeletal disorders                                                                                                                                                                                                                                                                                                                                                                                                                                                                                                                                                            | Skin disorders                                                                                                                                                                                                                                                                                                                                                                                                                                                                                                                                                                                                                                               |
|---------------------------------------------------------------------------------------------------------------------------------------------------------------------------------------------------------------------------------------------------------------------------------------------------------------------------------------------------------------------------------------------------------------------------------------------------------------------------------------------------------------------------------------------------------------------------------------------------------------------------------------------------------------------------------------------------------------------------------|---------------------------------------------------------------------------------------------------------------------------------------------------------------------------------------------------------------------------------------------------------------------------------------------------------------------------------------------------------------------------------------------------------------------------------------------------------------------------------------------------------------------------------------------------------------------------------------------|---------------------------------------------------------------------------------------------------------------------------------------------------------------------------------------------------------------------------------------------------------------------------------------------------------------------------------------------------------------------------------------------------------------------------------------------------------------------------------------------------------------------------------------------------------------------------------------------------------------------------------------------------------------------|
| 
 
• Cranial nerve disorders, including paralyses/paresis (e.g. Bell's palsy), and neuritis (e.g. optic neuritis)
 
• Multiple sclerosis (including variants)
 
• Transverse myelitis
 
• Guillain-Barré syndrome, (including Miller Fisher syndrome and other variants)
 
• Other demyelinating diseases (including acute disseminated encephalomyelitis)
 
• Myasthenia gravis (including Lambert-Eaton myasthenic syndrome)
 
• Non-infectious encephalitis/encephalomyelitis
 
• Neuritis (including peripheral neuropathies)
 
                                                                                               | 
 
• Systemic lupus erythematosus
 
• Scleroderma (including, CREST syndrome and morphoea)
 
• Systemic sclerosis
 
• Dermatomyositis
 
• Polymyositis
 
• Antisynthetase syndrome
 
• Rheumatoid arthritis,
 
• Juvenile chronic arthritis, (including Still's disease)
 
• Polymyalgia rheumatica
 
• Reactive arthritis
 
• Psoriatic arthropathy
 
• Ankylosing spondylitis
 
• Relapsing polychondritis
 
• Mixed connective tissue disorder
 
 | 
 
• Psoriasis
 
• Vitiligo
 
• Raynaud's phenomenon
 
• Erythema nodosum
 
• Autoimmune bullous skin diseases (including pemphigus, pemphigoid and dermatitis herpetiformis)
 
• Cutaneous lupus erythematosus
 
• Alopecia areata
 
• Lichen planus
 
• Sweet's syndrome
 
                                                                                                                                                                                                                                                                                   |
| Liver disorders                                                                                                                                                                                                                                                                                                                                                                                                                                                                                                                                                                                                                                                                                                          | Gastrointestinal disorders                                                                                                                                                                                                                                                                                                                                                                                                                                                                                                                                                           | Metabolic diseases                                                                                                                                                                                                                                                                                                                                                                                                                                                                                                                                                                                                                                           |
| 
 
• Autoimmune hepatitis
 
• Primary biliary cirrhosis
 
• Primary sclerosing cholangitis
 
• Autoimmune cholangitis.
 
                                                                                                                                                                                                                                                                                                                                                                                                                                                                                                                                      | 
 
• Crohn's disease
 
• Ulcerative colitis
 
• Ulcerative proctitis
 
• Celiac disease
 
                                                                                                                                                                                                                                                                                                                                                                                                                                 | 
 
• Autoimmune thyroiditis (including Hashimoto thyroiditis)
 
• Grave's or Basedow's disease
 
• Diabetes mellitus type I
 
• Addison's disease
 
                                                                                                                                                                                                                                                                                                                                                                                                                                               |
| Vasculitides                                                                                                                                                                                                                                                                                                                                                                                                                                                                                                                                                                                                                                                                                                             |                                                                                                                                                                                                                                                                                                                                                                                                                                                                                                                                                                                             | Others                                                                                                                                                                                                                                                                                                                                                                                                                                                                                                                                                                                                                                                       |
| 
 
• Large vessels vasculitis including: giant cell arteritis such as Takayasu's arteritis and temporal arteritis.
 
• Medium sized and/or small vessels vasculitis including: polyarteritis nodosa, Kawasaki's disease, microscopic polyangiitis, Wegener's granulomatosis, Churg–Strauss syndrome, thromboangiitis obliterans (Buerger's disease), necrotizing vasculitis, allergic granulomatous angiitis, Henoch-Schonlein purpura, anti-neutrophil cytoplasmic antibody positive vasculitis, Behcet's syndrome, leukocytoclastic vasculitis.
 
• Vasculitides secondary to other immune mediated diseases such as lupus vasculitis and rheumatoid vasculitis.
 
 |                                                                                                                                                                                                                                                                                                                                                                                                                                                                                                                                                                                             | 
 
• Autoimmune hemolytic anemia
 
• Autoimmune thrombocytopenias
 
• Antiphospholipid syndrome
 
• Pernicious anemia
 
• Autoimmune glomerulonephritis (including IgA nephropathy, glomerulonephritis rapidly progressive, membranous glomerulonephritis, membranoproliferative glomerulonephritis, and mesangioproliferative glomerulonephritis)
 
• Uveitis
 
• Autoimmune myocarditis/cardiomyopathy
 
• Sarcoidosis
 
• Stevens-johnson syndrome
 
• Sjögren's syndrome
 
• Idiopathic pulmonary fibrosis
 
• Goodpasture syndrome
 
 |

When there is enough evidence to make any of the above diagnoses, the AE must be reported as a pIMD. Symptoms, signs or conditions which might (or might not) represent the above diagnoses, should be recorded and reported as AEs but not as pIMDs until the final or definitive diagnosis has been determined, and alternative diagnoses have been eliminated or shown to be less likely.

In order to facilitate the documentation of pIMDs in the eCRF, a pIMD standard questionnaire and a list of preferred terms (PTs) and PT codes corresponding to the above diagnoses will be available to investigators at study start.

